## Abstract

**Background:**

Chronic obstructive pulmonary disease (COPD) is the end result of a susceptible individual being exposed to sufficiently deleterious environmental stimuli. More than 90% of COPD-related deaths occur in low- and middle-income countries (LMICs). LMICs face unique challenges in managing COPD; for example, deficient primary care systems present challenges for proper diagnosis and management. Formal diagnosis of COPD requires quality-assured spirometry, which is often limited to urban health centres. Similarly, standard treatment options for COPD remain limited where few providers are trained to manage COPD. The Global Excellence in COPD Outcomes (GECo) studies aim to assess the performance of a COPD case-finding questionnaire with and without peak expiratory flow (PEF) to diagnose COPD, and inform the effectiveness and implementation of COPD self-management Action Plans in LMIC settings. The ultimate goal is to develop simple, low-cost models of care that can be implemented in LMICs. This study will be carried out in Nepal, Peru and Uganda, three distinct LMIC settings.

**Methods/design:**

We aim to assess the diagnostic accuracy of a simple questionnaire with and without PEF to case-find COPD (GECo1), and examine the effectiveness, cost-effectiveness and implementation of a community-health-worker-supported self-management Action Plan strategy for managing exacerbations of COPD (GECo2). To achieve the first aim, we will enrol a randomly selected sample of up to 10,500 adults aged ≥ 40 years across our three sites, with the goal to enrol 240 participants with moderate-to-severe COPD in to GECo2. We will apply two case-finding questionnaires (Lung Function Questionnaire and CAPTURE) with and without PEF and compare performance against spirometry. We will report ROC areas, sensitivity and specificity. Individuals who are identified as having COPD grades B–D will be invited to enrol in an effectiveness-implementation hybrid randomised trial of a multi-faceted COPD self-management Action Plan intervention delivered by CHWs. The intervention group will receive (1) COPD education, (2) facilitated-self management Action Plans for COPD exacerbations and (3) monthly visits by community health workers. The control group will receive COPD education and standard of care treatment provided by local health providers. Beginning at baseline, we will measure quality of life with the EuroQol-5D (EQ-5D) and St. George’s Respiratory Questionnaire (SGRQ) every 3 months over a period of 1 year. The primary endpoint is SGRQ at 12 months. Quality-adjusted life years (QALYs) using the Short-Form 36 version 2 will also be calculated. We will additionally assess the acceptability and feasibility of implementing COPD Action Plans in each setting among providers and individuals with COPD.

**Discussion:**

This study should provide evidence to inform the use of pragmatic models of COPD diagnosis and management in LMIC settings.

**Trial registration:**

NCT03359915 (GECo1). Registered on 2 December 2017 and NCT03365713 (GECo2). Registered on 7 December 2017. Trial acronym: Global Excellence in COPD Outcomes (GECo1; GECo2).

**Electronic supplementary material:**

The online version of this article (10.1186/s13063-018-2909-8) contains supplementary material, which is available to authorized users.

## Background

### The global importance of COPD

Chronic obstructive pulmonary disease (COPD) is ‘*a common, preventable and treatable disease that is characterized by persistent respiratory symptoms and airflow limitation that is due to airway and/or alveolar abnormalities usually caused by significant exposure to noxious particles or gases*’ [1]. The primary risk factor for COPD in high-income countries (HICs) is tobacco smoke exposure; however, household air pollution (HAP), from burning solid fuels such as wood, dung, agricultural crop waste, and coal for energy, is the primary risk factor for COPD in low- and middle-income countries (LMICs) [2]. In addition to chronic progressive symptoms and functional impairment, some individuals with COPD are prone to intermittent deteriorations in respiratory health, or ‘exacerbations’, often driven by infection [3]. The global burden of COPD is large and increasing. In 2015, it was estimated that 174 million people worldwide had clinically significant COPD, and an estimated 3.2 million individuals died from the disease, an increase of 11.6% since 1990 [4]. COPD will become the third leading cause of death by 2030 [5]. Prevalence estimates vary due to different methods of diagnosis; however, the BOLD studies report a prevalence of moderate COPD or higher to be around 10% globally [1, 6]. Exacerbations are a major source of morbidity from COPD, and the cause of direct healthcare costs in high-income countries [7].

### COPD in LMICs

More than 90% of COPD-related deaths occur in LMICs [8]. The economic cost of illness due to COPD among LMICs was estimated to be US$1 trillion in 2010 and is expected to increase to US$2.6 trillion by 2030 [9]. Indirect costs, including loss of productivity both by individuals affected by COPD and their caregivers, are important in LMICs [9]. LMICs face unique challenges when addressing COPD, including poorly resourced primary care systems and trained workforce shortages, which present challenges with COPD diagnosis and management, especially during exacerbations [10]. The chronic nature of COPD means that people may access multiple healthcare providers, including alternative providers.

### COPD case finding

The ‘gold standard’ method for diagnosis of COPD is quality-assured, post-bronchodilator spirometry, though COPD represents a range of phenotypes with different symptomatic presentations including shortness of breath, cough and sputum production [1]. In LMICs this is often only available from pulmonary physicians in specialised urban centres, while most of the burden associated with this condition occurs in rural areas [10]. A number of COPD case-finding questionnaires have been validated in HIC settings, which are, therefore, likely to be more sensitive to tobacco-associated COPD than biomass-fuel smoke [11–13]. In 2010, Yawn et al. developed and validated a simple five-item Lung Function Questionnaire (LFQ) and compared this to standard spirometry (area under the curve (AUC) = 0.720 with sensitivity and specificity of 73.2 and 58.2%, respectively) [11]. Martinez et al. combined peak expiratory flow (PEF) measurements with a case-finding instrument to improve the sensitivity, specificity and AUC for detecting COPD (89.7%, 78.1%, 0.795, respectively) [12]. Case-finding instruments combined with low-cost peak-flow meters could be useful tools for identifying individuals who should be further screened for COPD in LMIC settings as well, although this has not been previously tested.

### COPD self-management

Written self-management Action Plans are an integral part of evidence-based management of COPD according to international guidelines [1]. Action Plans support people with COPD to recognise and react appropriately to exacerbations through initiation of additional pharmacotherapy and modification of healthcare-seeking behaviours [14]. A number of studies and systematic reviews have tested self-management interventions for prevention and successful treatment of COPD exacerbations in high-income settings [15–19]. Bourbeau et al. demonstrated a 39.8% reduction in hospitalisations for exacerbations of COPD in a multicentre randomised control trial of self-management with comprehensive patient education compared to usual care [14]. A similar trial by Effing et al. reviewed the effectiveness of self-management on the severity of exacerbations and found a trend to fewer exacerbation days [20]. Finally, a 2005 Cochrane Review found that Action Plans aid people with COPD in recognising severe exacerbations and reacting appropriately to an exacerbation via the self-initiation of antibiotics and/or orally administered steroids [16]. The potential benefits, cost-effectiveness and implementation challenges of Action Plans in LMIC have not previously been studied.

Efforts to scale-up COPD case finding and management are hampered by a shortage of specialised healthcare providers. Healthcare workforce shortages have been well documented among LMICs and community health worker (CHW) models of care have been widely utilised in health priority areas including infectious diseases and nutritional interventions [10, 21]. CHWs are a diverse category of health workers who commonly work in communities outside of fixed health facilities and have formal, but limited, training for the tasks they perform [21]. CHWs can serve as a bridge between people and healthcare systems [22]. Many LMICs have existing CHW networks and a long history of implementing public health interventions utilising CHWs to deliver health services [21]. CHWs are uniquely qualified as connectors and tools of empowerment in chronic disease management because they live within the community in which they work [22–24].

Given the high and rising global burden of COPD, better strategies to diagnosis COPD and manage exacerbations are urgently needed for LMICs. In two linked studies (Global Excellence in COPD Outcomes: GECo1 and GECo2), we aim to validate a modified COPD case finding questionnaire (with and without PEF) to better identify individuals for further screening for COPD, as well as to develop evidence to support the wider implementation of COPD Action Plans among CHWs, allowing for simple, low-cost models of COPD care in LMICs. This study will enrol individuals in three distinct LMIC regions, namely Nepal, Peru and Uganda.

## Method / design

### Goals

The over-arching goal of the GECo studies is to develop simple, cost-effective models of COPD care that can be implemented in LMICs. An overview of the studies is shown in Fig. 1. Their schedule of enrolment, interventions and assessments in shown in Fig. 2.

**Fig. 1 Fig1:**
[figure not shown]
Overview of the GECo Studies

**Fig. 2 Fig2:**
[figure not shown]
Schedule of enrolment, interventions and assessments

### Objectives

The objectives of the present study are to validate case-finding instruments with and without peak-flow measurements in three diverse LMIC settings, and to develop evidence supporting the effectiveness, cost-effectiveness and implementation of a CHW-based strategy to deliver self-management Action Plans for COPD.

### Research questions

#### Primary research questions

GECo1: What is the diagnostic accuracy of case finding for COPD using a questionnaire with and without peak-flow measurements, compared to gold-standard spirometry?GECo2: What is the effect of a multi-faceted intervention comprising a self-directed COPD Action Plan delivered and supported by CHWs for the management of COPD exacerbations on respiratory health, and is this intervention likely to be implementable and cost-effective?

#### Implementation research questions

GECo1: What is the appropriateness, acceptability and feasibility of using questionnaires to identify COPD cases from the perspective of local community members, community health workers, local health centre physicians and Ministries of Health?GECo2: What is reach, adoption, implementation and maintenance of a self-directed COPD Action Plan strategy for management of COPD exacerbations?GECo2: How does the value for money of the self-directed COPD Action Plan strategy vary by different implementation constraints and for different socioeconomic sub-groups?

### Study design overview

#### GECo1

For the *Case-finding study* (GECo1) we will test the diagnostic accuracy of case-finding instruments in LMIC settings. To achieve the aim we will enrol a representative community sample of up to 10,500 adults of 40 years of age and above in Nepal, Peru and Uganda (Fig. 2). We will apply two modified questionnaires, with and without PEF measurements, and compare performance of this testing to spirometry, which will be conducted in the field according to the American Thoracic Society/European Respiratory Society (ATS/ERS) standards using Easy-on-Air spirometers (ndd, Zurich, Switzerland). The primary endpoint is area under the receiver operating characteristics (ROC) curve. We will report the sensitivity, specificity and ROC of case-finding instrument with and without PEF compared to standard spirometry.

#### GECo2

For the *Self-management trial* (GECo2), we will randomise 240 adults (total for all sites) with grades B–D COPD as per the GOLD 2017 classification, identified in the case-finding phase, to an intervention or control arm. We will develop and test a locally adapted, CHW-based intervention strategy to improve self-management of COPD (see ‘Description of intervention’). CHWs will be instructed on chronic disease management for COPD, and how to utilise the self-management Action Plan for management of exacerbations. We will measure quality of life with the EuroQol-5D (EQ-5D) and St. George’s Respiratory Questionnaire (SGRQ) every 3 months over a period of 1 year. The primary efficacy endpoint is the change in the SGRQ at 12 months. Results of the EQ-5D will be used to calculate quality-adjusted life years (QALYs) which will inform the analysis of the cost-effectiveness and equity impacts of implementation. We will additionally assess the reach, adoption, implementation and maintenance of Action Plans for exacerbations in each setting.

### Settings

The study settings represent three distinct geographic and economic regions in Asia, Latin America and Sub-Saharan Africa. Inclusion of these countries will allow us to assess varying degrees of urbanisation, environmental exposures (i.e. tobacco and biomass-fuel smoke), and varying implementation contexts.

*Nepal* is a low-income country located in Southeast Asia with a total population of 26.5 million, of which 82% is rural. Nepal’s GDP is £49 billion, with 25% of the population living below the national poverty line. The current ratio of physicians per person is 1:1742. The current minimum wage is Rs 9700 per month (£66). The study site is in Bhaktapur, 8 miles east of Kathmandu. The majority of the estimated 80,000 inhabitants of Bhaktapur municipality are either craftsman or businessmen, while many migrants come to work in the outskirts at brick or carpet factories. CHWs, called female community health volunteers (FCHVs), are volunteers coordinated by the Bhaktapur municipality to promote community-based healthcare, health education and referrals. FCHVs are trained by their District Public Health Office, under the Ministry of Health to serve within their respective communities, mainly on family planning, vaccination and nutrition programmes. There are approximately 90 FCHVs active in the municipality of Bhaktapur and over 52,000 throughout Nepal.

*Peru* is an upper-middle-income country located in South America with a population of 30.5 million, 10 million of whom live in the capital (Lima), and 78.6% of whom live in urban areas. Peru’s GDP is £145 billion, and 26% of the population lives below the national poverty line. The current ratio of physicians per person is 1:1116. The minimum wage in Peru is 850 soles per month (£186). We will conduct this study in Pampas de San Juan de Miraflores, a peri-urban community in southern Lima, Peru’s capital. CHWs or ‘*agentes comunitarios*’ include community members who volunteer to support health education programmes and campaigns at their corresponding health centre. The size of CHW networks and specific duties and responsibilities can vary considerably depending on the region, district, or health centre.

*Uganda* is a low-income country located in East Africa with a total population of 37 million, and a large rural population (> 80%). Uganda’s GDP is £19 billion with 19.5% living below the national poverty line. The study will be carried out in the Nakeseke District of Uganda. Most of the inhabitants (75%) are subsistence farmers and over 60% of them live on less than 45,000 shillings (£9) per month. The current ratios of physicians and nurses per person are 1:25,000 and 1:5000, respectively, making Nakeseke one of the most under-resourced health districts in Uganda. CHWs called Village Health Teams (VHTs) are selected in each village by the Uganda Ministry of Health. They provide formal referral services to local health centres and assist with community-based follow-up. The VHT consist of community members who volunteer for the position and are trained by the Uganda Ministry of Health.

### Study populations

We will enrol an age- and sex-stratified random sample of full-time residents of the proposed study areas in Nepal, Peru and Uganda using existing census data. Inclusion criteria are: aged ≥ 40 years; capable of performing spirometry; and being a full-time resident of the community. Full-time residence will be defined as having lived in the study area for more than 6 months. Exclusion criteria are: self-reported pregnancy; having active pulmonary tuberculosis or being on medications for pulmonary tuberculosis; unable to do spirometry because of eye surgery, thoracic surgery, abdominal surgery, or myocardial infarction in the 3 months prior to study visit or a blood pressure > 180/100 mmHg. For the self-management component of the trial, we will enrol individuals who were identified to have grades B–D COPD [1].

### Procedures case-finding phase (GeCo1)

#### Data collection

Demographic questionnaires will be applied to obtain socioeconomic information, exposure history to cigarettes and household air pollution, medical history and family history of respiratory illness. Data will be collected by trained field workers at each site and will be electronically entered into REDCap using tablets with GPS capability (Asus Z380M ZenPad, Taipei, Tawain) [25].

##### Lung Function Questionnaire (LFQ)

We will administer an instrument context-adapted from the original LFQ, which has been validated in high-income countries, and apply it to LMIC settings [11]. The LFQ assesses five items: age, smoking history, wheeze, dyspnoea and phlegm. The modified questionnaire will include additional items including exposure to biomass fuel and will be administered by field workers (see Additional file 1).

##### Capture

CAPTURE is a simple five-item questionnaire which, together with PEF, has been shown to be a viable approach for COPD case identification in the US in primary care settings [12]. CAPTURE with PEF can identify COPD patients who would benefit from currently available therapy and require further diagnostic evaluation, and we will use this validated instrument and apply it to LMIC. CAPTURE assesses five items: environmental exposure, sensitivity to air quality/weather, how breathing interferes with physical activities, comparing health with peers, and exacerbations.

##### *MRC Dyspnoea Scale and COPD Assessment Test* (CAT)

At the case-finding visit, participants will be asked to complete the modified Medical Research Council Dyspnoea Score (mMRC) and the COPD Assessment Test (CAT), which have been translated into relevant local languages and previously validated. The mMRC categorises self-perceived disability among those with COPD on a five-item scale. The CAT is designed to measure the impact of COPD on a person’s well-being and daily life and is measured with eight items on a 40-point scale and will be administered to those with COPD on spirometry.

##### Anthropometry and spirometry

All participants will have blood pressure, weight and standing height and spirometry performed**.** Anthropometric measurements will be recorded in triplicate and the median measurements will be used for analysis. Systolic and diastolic blood pressure measurements on the second and third measurements will be averaged to calculate blood pressure; the first measurement will be ignored to avoid potential white-coat hypertension.

Trained study fieldworkers will conduct spirometry using a flow-based portable spirometer to measure pulmonary function and will record forced vital capacity (FVC), forced expiratory volume in 1 s (FEV_1_), the percentage of FVC exhaled in the first second (FEV_1_/FVC), and flow-volume curves. We will obtain at least three acceptable manoeuvres in accordance with ATS/ERS guidelines [26]. We will use the Global Lung Function Initiative mixed ethnic population reference for calculation of percentage predicted values or Z-scores [27]. We will test for reversibility (increase in FEV_1_ of ≥ 12% and increase in FEV_1_ ≥ 200 mL) with two puffs from a salbutamol inhaler (90 mcg/puff) via a spacer. A COPD diagnosis will be defined as post-bronchodilator FEV_1_/FVC below the lower limit of normal for that population following ATS/ERS standardised guidelines [26].

##### Spirometry quality control

All spirometry will be read by two independent reviewers locally who have been trained in spirometry per ATS/ERS guidelines [27]. Spirometry that is deemed not acceptable or reproducible will be repeated up to one additional time. If there is discrepancy in local reviewers over reads, the spirogram in question will be reviewed centrally. Additionally, 10% or all curves will be independently reviewed centrally for site-specific quality control. Spirometry will be graded according to ATS/ERS classification and only high- quality spirometry will be included for analysis and trial recruitment [28].

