#### Sample size and data analysis

##### Sample size

The sample size required to estimate the ROC area within 1.5% (based on a 95% confidence interval), assuming an anticipated sensitivity of 90% and specificity of 60%, and assuming 11% of those screened will have COPD is 9669 participants [2, 29]. To ensure an adequate sample size is subsequently available for GECo2, we will recruit a total of up to 10,500 subjects (3500 at each site).

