##### Analysis

By site and overall we will summarise the characteristics of those consenting to the study including demographics, exposure history to tobacco and/or household air pollution, anthropometric measurements, spirometry measurements (FEV_1_, FVC and FEV_1_/FVC ratio) and lung function scores (mLFQ, Capture, mMRC dyspnoea scores).

Using a receiver operating characteristic (ROC) area analysis, we will examine the diagnostic accuracy of the questionnaire scores in identifying cases of COPD (compared to spirometry). Curves will be obtained for the mLFQ and CAPTURE questionnaires alone and then each with addition of the PEF scores. Logistic regression models will be used to obtain the ROC curve and area (AUC), with 95% confidence interval. Estimates will be weighted based on census information from each site to better reflect the population. A comparison between the ROC areas will be made by site.

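### GECo1 accuracy is analysed only in participants with high-quality spirometry, and no check or correction is described for those excluded; sensitivity and specificity are biased if usability depends on symptom score or PEF

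*Protocol article*

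**What the plan says.** The section Spirometry quality control of the protocol article has every spirogram graded and then fixes the analysis set: "only high- quality spirometry will be included for analysis and trial recruitment". Before exclusion there is one further attempt: "Spirometry that is deemed not acceptable or reproducible will be repeated up to one additional time". Study populations already limits entry to people "capable of performing spirometry".

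The GECo1 Analysis section compares the modified LFQ and CAPTURE, each with and without PEF, against spirometry. The only adjustment it describes is this: "Estimates will be weighted based on census information from each site to better reflect the population". It does not name the census variables; the sample itself is stratified by age and sex.

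On endpoints, the GECo1 design overview says: "The primary endpoint is area under the receiver operating characteristics (ROC) curve". The Abstract and that overview also commit to reporting sensitivity and specificity.

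**The concern.** Insisting on a good reference test is right. The difficulty is what follows: people without a usable reference drop out of the accuracy estimates, and the rest are weighted back to the community by census data.

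This does no harm to sensitivity and specificity if, among people with COPD and among people without it, usability is unrelated to the index test. A relation is plausible. PEF and spirometry are both forced expirations, and the questionnaires score items such as dyspnoea, wheeze, phlegm and limitation of activity by breathing. If such a relation exists, the error is a bias and recruiting more people does not shrink it. At stake are the two figures a health service would use to judge how many cases the tool finds and how many people it sends on needlessly.

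**Working it through.** **Inputs from the article (GECo1 Sample size).** Anticipated sensitivity 0.90, specificity 0.60, prevalence 11%, ROC area to within 0.015 (95% interval), 9669 participants required, up to 10,500 recruited.

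**Assumed.** The usable share is v1 in screen-positives and v0 in screen-negatives, at one cutpoint. The article gives no values for these.

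**The plan's own figure.** 9669 was not reproduced exactly. The nearest variant was the Obuchowski binormal variance with a = z(0.90) + z(0.60) = 1.535, which gives 9964, about 3% higher. The method is only cited, so this is not held against the plan, and the bias results below do not use it.

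**Complete-case formulas.**
- Observed sensitivity = 0.9·v1 / (0.9·v1 + 0.1·v0)
- Observed specificity = 0.6·v0 / (0.6·v0 + 0.4·v1)

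| v1 / v0 | Sensitivity | Specificity |
|---|---|---|
| 80% / 95% | 0.720/0.815 = 88.3% | 0.570/0.890 = 64.0% |
| 85% / 95% | 0.765/0.860 = 89.0% | 0.570/0.910 = 62.6% |
| 90% / 95% | 0.810/0.905 = 89.5% | 0.570/0.930 = 61.3% |
| 95% / 85% (reverse) | 0.855/0.940 = 91.0% | 0.510/0.890 = 57.3% |

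If usability depends on COPD status alone (for example 80% in cases, 95% in non-cases), the shares cancel within each group and the result stays at 90% and 60%.

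**Shift against sampling error** (simple binomial, all 10,500 enrolled, at 80%/95%).
- Specificity: analysed non-cases = 10,500 × 0.89 × 0.89 = 8317. Half-width = 1.96·√(0.640·0.360/8317) = 1.0 point. The shift is 4.0 points (2.6 points at 85%/95%).
- Sensitivity: analysed cases = 10,500 × 0.11 × 0.815 = 941. Half-width = 1.96·√(0.883·0.117/941) = 2.1 points. The shift is 1.7 points.

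The specificity interval would miss the true value; the sensitivity interval would still contain it.

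**Primary endpoint.** Take a continuous score, N(0,1) in non-cases and N(1.535,1) in cases, so AUC = 0.861. Let usability change smoothly (logistic, slope 2, centred at the cutpoint) from a level at low scores to a level at high scores.

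| Low → high score | AUC | Change from 0.8613 |
|---|---|---|
| 95% → 85% | 0.8623 | +0.0010 |
| 95% → 80% | 0.8628 | +0.0015 |
| 90% → 60% | 0.8639 | +0.0026 |
| 85% → 95% | 0.8600 | −0.0013 |

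Each change is small against 0.015. In this smooth model the cutpoint measures also move less: at 95% → 80%, sensitivity is 0.8905 and specificity 0.6225. The cruder one-cutpoint summary, (sensitivity + specificity)/2, moves more: from 0.750 to 0.762 at 80%/95%, and to 0.775 at 60%/90%.

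**Does reweighting repair it?** When usability depends only on the test result, dividing each cell by its usable share recovers the truth. At 80%/95%, 0.720/0.80 = 0.90 and 0.095/0.95 = 0.10, so sensitivity returns to 90%; specificity returns to 60% in the same way. When usability depends on COPD status alone (80%/95%), reweighting by test result gives 90.3% and 59.2%, a small error where complete-case analysis had none.

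**The case against.** The strongest reply is that this is a condensed article. The full protocol and SAP are not shown, and handling of unusable reference tests is ordinary SAP content. A reader might infer that GECo1 will be analysed with no correction at all. The article does not support that; it supports only that none is described. What remains is that the analysis set is stated, not left open, and the one adjustment named alongside it does not address this selection. For GECo2 the same article does set out how a missing outcome will be examined, though that does not prove GECo1 lacks a plan.

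Second, a reader might infer that specificity will look better than it is. Nothing in the article gives a rate of unusable spirometry or links it to symptoms or PEF. The reverse pattern lowers specificity to 57.3%.

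Third, eligibility, the repeat attempt and central review of discrepant reads all reduce losses, and census weights that include age would absorb any part of the selection that runs through age. This stands. However, grading, repeating and excluding tests presupposes some failures among enrolled people, and none of these steps makes the failures random.

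Fourth, it is tempting to add a shortfall in sample size, since the margin over 9669 is (10,500 − 9669)/10,500 = 7.9% and is explained by the needs of GECo2. The article does not say that 9669 is the number after exclusions. Even on that reading, 9258 analysed (80%/95%) gives a half-width of 0.015·√(9669/9258) = 0.0153, and 9497 (85%/95%) gives 0.0151. That is immaterial.

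Finally, the primary endpoint is ROC area, which is little affected. This stands and sets the scope of the point.

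**Conclusion.** The point holds in conditional form. The article fixes a complete-case rule for the reference standard and describes only census weighting. If usability depends on score or PEF given COPD status, sensitivity and specificity are biased. Under the assumed shares of 80–90% in screen-positives and 95% in screen-negatives, sensitivity falls by 0.5 to 1.7 points and specificity rises by 1.3 to 4.0 points. With 95% and 85% the shifts are +1.0 and −2.7 points. They are smaller if usability changes smoothly with the score, and nil if it depends on COPD status alone.

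The shares are assumptions, and neither size nor direction can be settled from the article. ROC area changes by about 0.003 or less in the continuous-score model, so the primary endpoint is not seriously threatened. The concern is mainly the sensitivity and specificity that the study undertakes to report.

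**What to change.** Keep high-quality spirometry as the reference standard, and keep the complete-case estimate. Pre-specify one added analysis that multiplies the census weights by the inverse of the estimated probability of usable spirometry, modelled on site, age, sex, questionnaire score and PEF. Report it beside the complete-case result, with the percentage excluded by score band and PEF band. That table alone would show whether usability varies with the index test.

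The cost is a little more analysis on data the study already plans to collect, slightly wider intervals, and an assumption that usability is ignorable given the modelled variables. The assumption is a real one: if usability also depends on COPD status beyond those variables, the reweighted estimate carries some bias of its own, which is why both results should be shown.
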